## Abstract

**Background:**

Stroke is the prime cause of morbidity and mortality in the general population, and hypertension will increase the recurrence and mortality of stroke. We report a protocol of a pragmatic randomized controlled trial (RCT) using blood pressure (BP)-lowering acupuncture add-on treatment to treat patients with hypertension and stroke.

**Methods:**

This is a large-scale, multicenter, subject-, assessor- and analyst-blinded, pragmatic RCT. A total of 480 patients with hypertension and ischemic stroke will be randomly assigned to two groups: an experimental group and a control group. The experimental group will receive “*HuoXueSanFeng*” acupuncture combined with one antihypertensive medication in addition to routine ischemic stroke treatment. The control group will only receive one antihypertensive medication and basic treatments for ischemic stroke. *HuoXueSanFeng* acupuncture will be given for six sessions weekly for the first 6 weeks and three times weekly for the next 6 weeks. A 9-month follow-up will, thereafter, be conducted. Antihypertensive medication will be adjusted based on BP levels. The primary outcome will be the recurrence of stroke. The secondary outcomes including 24-h ambulatory BP, the TCM syndrome score, the Short Form 36-item Health Survey (SF-36), the National Institute of Health Stroke Scale (NIHSS), as well as the Barthel Index (BI) scale will be assessed at baseline, 6 weeks and 12 weeks post initiating treatments; cardiac ultrasound, carotid artery ultrasound, transcranial Doppler, and lower extremity ultrasound will be evaluated at baseline and 12 weeks after treatment. The safety of acupuncture will also be assessed.

**Discussion:**

We aim to determine the clinical effects of controlling BP for secondary prevention of stroke with acupuncture add-on treatment.

**Trial registration:**

ClinicalTrials.gov, ID: NCT02967484. Registered on 13 February 2017; last updated on 27 June 2017.

**Electronic supplementary material:**

The online version of this article (doi:10.1186/s13063-017-2171-5) contains supplementary material, which is available to authorized users.

## Background

Worldwide, stroke is a leading cause of death and disability [1–3]. A patient with a history of stroke is more vulnerable to recurrence [4, 5]^.^ Especially in China, the recurrence rate of stroke is higher than that of western countries [6, 7]. Recurrent stroke demonstrates higher mortality and disability rates than the previous stroke, which is a heavy burden on both health care resources and society in general [7, 8]. Ischemic stroke is the most common type of stroke and 72.7% of Chinese ischemic stroke patients also suffer from hypertension [6], an independent risk factor for stroke recurrence [9]. Therefore, it would be of great benefit in combating stroke recurrence to decrease blood pressure (BP).

Antihypertensive medications have been regularly used to reduce BP; however, low adherence to antihypertensive medications is prevalent due to various factors including prior experience of medication side effects [10], leading to poor BP control [11]. Uncontrolled BP maybe related to side effects or interactions of antihypertensives and this observation is more commonly noted in older populations [12, 13]. Moreover, a former meta-analysis has shown that only angiotensin-converting enzyme inhibition (ACEI) plus diuretics significantly decreases recurrent stroke events, and no significant association between BP reduction and all adverse outcomes was found [14]. It is apparent that the benefit of ACEI plus diuretics for secondary prevention of stroke is explained by mechanisms beyond the effects of lowering BP alone. The underlying mechanisms may be the divergent cardiovascular effects of ACEI [15], and the ability of diuretics to reduce proteinuria and protect the vascular endothelium [16]. Additionally, the presence of a J-shaped relationship between BP and risk of recurrent stroke is, to a certain degree, confirmed by previous research [17]. Under this context, in order to effectively regulate BP for reducing stroke recurrence, it is urgent to find an alternative that will affect multiple targets.

Acupuncture, with a long history of development in Chinese medicine, is becoming the focus of clinical researchers as an alternative for treating hypertension [18, 19]. Acupuncture-induced regulation of BP has been found to involve peripheral and central neural systems [20] and immune modulation mechanisms [21]. Its multiple-target features might explain the potential of acupuncture in effectively regulating BP to reduce stroke recurrence.

The synergistic BP-lowering effectiveness of acupuncture and antihypertensive agents has been proven, despite there formerly being insufficient evidence for acupuncture alone in lowering BP [22]. Recently, researchers have reported some positive results regarding sole acupuncture treatment for hypertension [23–25]. The reasons for this paradoxical situation could be disparities in acupuncture manipulation skills as well as other technical factors. Considering the limited reporting quality, the effect of pure acupuncture in lowering BP remains elusive.

Given that complementary and alternative interventions are recommended for mild and moderate hypertensive patients [26], we cautiously decided to select the hypertensive patients with uncontrolled BP (systolic BP ≥ 140 and < 160, or/and diastolic BP ≥ 90 and < 100 mmHg) who were taking one class of antihypertensive drugs to be the participants. The difference between the control and experimental groups is that in our experimental group, after a period of BP-lowering acupuncture add-on treatment, i.e., the “*HuoXueSanFeng*” needling method which has been proved to positively treat primary hypertension [27–33], if the BP falls below 140/90 mmHg, the prior antihypertensive drugs will be ceased, so as to observe the clinical effects of pure acupuncture on BP. Moreover, aiming to create a situation that is analogous to the real world, antihypertensive drugs will be adjusted based on the patients’ BP readings (detailed in the “Antihypertensive medication adjustment” section below) in both groups, respectively.

Altogether, our team conceived this high-quality, pragmatic randomized controlled clinical trial with the primary objective to determine whether BP-lowering acupuncture add-on therapy could decrease the recurrence of first-time ischemic stroke in patients during the 9-month follow-up period.

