### Interventions (Table 2)

**Table 2 Tab2:** Protocol form

Item	Control group	Experimental group
Aim	To testify the efficacy of the acupuncture method of *HuoXueSanFeng* on stroke recurrence among ischemic stroke patients with hypertension	
Interventions	1 type of antihypertensive drug (may be adjusted based on the BP levels) + *XingNaoKaiQiao* acupuncture method + other routine care for stroke	*HuoXueSanFeng* acupuncture method + *XingNaoKaiQiao* acupuncture method + 1 type of antihypertensive drug (may be adjusted based on the BP levels) + other routine care for stroke
Intervention time	Continuous treatment period: 6 times a week, 6 weeks Consolidation treatment period: three times a week, 6 weeks	
Observation time	Before treatment, 6 weeks, 12 weeks, 24 weeks, and 48 weeks after treatment	
Researchers	To ensure the optimal effects of acupuncture stimulation, our therapists will be required to have clinical experience of acupuncture treatments for at least 8 years	
Materials	Disposable, sterile needles, 0.25 mm in diameter and 40 mm in length (HWATO, Suzhou, China)	

*BP* blood pressure

Both groups receiving acupuncture treatments ensures the blinding of subjects.

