### Antihypertensive medication adjustment

After randomization, an electronic BP machine and a BP diary notebook will be delivered to all patients for measuring and recording their BP levels. During the first 6-week inpatient treatments, they will be instructed how to use the machine accurately. BP will be measured within 1 h after morning waking before taking antihypertensive medications, at 3 h after taking antihypertensive medications, at 4 p.m. and before bedtime over the entire process. On each occasion, three repeated measurements of supine BP, following a rest of at least 15 min, will be conducted at 1-min intervals. The antihypertensive medication classes in both groups will be recorded. Lifestyle advice regarding hypertension and stroke will be given to the patients. In the experimental group, if the patients have a mean BP level below 140/90 mmHg for three consistent days, they will receive solely acupuncture treatment; thereafter, once their BP levels increase to ≥ 140 mmHg systolic and/or ≥ 90 mmHg diastolic for 1 month, prior antihypertensive medications should be re-dispensed. Otherwise, if BP levels are ≥ 160 mmHg systolic and/or ≥ 100 mmHg diastolic for three consistent days after initiating *HuoXueSanFeng* acupuncture treatments or over the follow-up period, additional antihypertensives should be prescribed. All the medication adjustments will be filled out in the Case Report Forms (CRFs).

For the control group, when the average systolic BP increases to ≥ 160 mmHg and/or diastolic BP ≥ 100 mmHg lasting for three continuous days in the study period, other antihypertensive drugs will be prescribed in the opinion of the treating physicians, and these will be documented for final analyses.

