The acupuncture method of *XingNaoKaiQiao* for the treatment of stroke was launched in 1972 by the first, and to date, only Chinese academician of engineering in the acupuncture discipline, [name], who devoted himself to introducing acupuncture to the whole world and developed an international academic team that cooperates with Germany, France, Japan, and Singapore, among other countries. For its internationally substantial contributions, *XingNaoKaiQiao* needling therapy for stroke has been recognized as another special acupuncture technique in addition to acupuncture anesthesia by foreign health care researchers. Besides the confirmed effects for stroke by our own team, the others also reported its encouraging results for stroke patients [38]. With the great success of *XingNaoKaiQiao*, academician [name] gained deeper insight into secondary stroke prevention, and established another acupuncture treatment for hypertension called *HuoXueSanFeng*, the BP-lowering acupuncture regimen used in our trial. Our previous researches have shown that this acupuncture method reduces BP for primary hypertension patients, and its immediate and long-term antihypertensive efficacy is significant for either BP-lowering or improving the patients’ clinical symptoms [27–33]. So, here we also want to investigate the BP-controlling effect of *HuoXueSanFeng*, especially regarding its sole efficacy, in a larger sample size population. In this study, both *XingNaoKaiQiao* and *HuoXueSanFeng* needling therapy are performed over the 12-week treatment period; *XingNaoKaiQiao* therapy is a general treatment for stroke with a high credibility, its free treatment here will enhance adherence with participation. Additionally, because both groups are needled, subject blinding should be ensured, minimizing the placebo effect of acupuncture.

Of note, in our trial, we cautiously selected three secondary endpoints, namely, Hcy, sCD40L, and copeptin levels, which were closely related to stroke recurrence. Elevated Hcy levels have been reported to be indicative of an increased risk for ischemic strokes and recurrent strokes [39]. sCD40L appears to be an independent predictor for stroke recurrence [40]. Copeptin has been studied to be a predictor of both severity at admission and 1-year stroke recurrence in stroke patients [41]. Assessing the influence of our study treatment on them might be reflective of the effects on stroke recurrence via acupuncture lowering hypertension.

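### Antihypertensives are stopped below 140/90 mmHg in the experimental arm only, so the randomised comparison is between two management strategies and isolates neither the add-on effect nor a sole-acupuncture effect

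*Protocol article*

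**What the plan says.** The Background gives the primary objective as to "determine whether BP-lowering acupuncture add-on therapy could decrease the recurrence of first-time ischemic stroke in patients during the 9-month follow-up period". The Abstract likewise describes the experimental treatment as acupuncture combined with one antihypertensive, adjusted to BP.

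The Background also presents drug stopping as what separates the arms: "The difference between the control and experimental groups is that in our experimental group, after a period of BP-lowering acupuncture add-on treatment", a BP below 140/90 mmHg means that "the prior antihypertensive drugs will be ceased, so as to observe the clinical effects of pure acupuncture on BP". The Antihypertensive medication adjustment section sets out the rules:

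- **Experimental, stopping:** "if the patients have a mean BP level below 140/90 mmHg for three consistent days, they will receive solely acupuncture treatment".
- **Experimental, restarting:** after readings at or above 140 systolic and/or 90 "diastolic for 1 month, prior antihypertensive medications should be re-dispensed".
- **Experimental, escalation:** further drugs at or above 160 and/or 100 mmHg for three days, including during follow-up.
- **Control:** escalation only. "For the control group, when the average systolic BP increases to ≥ 160 mmHg and/or diastolic BP ≥ 100 mmHg lasting for three continuous days", other drugs are prescribed. There is no stopping rule.

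The Discussion adds an interest in the BP effect of the needling, "especially regarding its sole efficacy, in a larger sample size population". Beneath Table 2 the article states: "Both groups receiving acupuncture treatments ensures the blinding of subjects".

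**The concern.** An add-on effect is the effect of adding acupuncture while background drugs are handled alike in both arms. Here they are handled differently by design. Escalation is common to both arms, but stopping and restarting belong to one. Any difference in recurrence, ambulatory BP or diary BP therefore mixes the effect of acupuncture with the effect of the stopping rule.

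The sole-acupuncture aim has a further problem. The patients who would show it are identified after randomisation by their own low BP, and the design has no drug-free comparator for them.

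At stake is what may be concluded. As worded, the article invites conclusions about add-on efficacy and sole efficacy that the randomised comparison does not by itself deliver.

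**Working it through.** **1. The plan's own figure.** Inputs from Sample size and statistical methods: 7% versus 16%, two-sided 5%, 80% power.

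n = [1.96·√(2·p̄·(1−p̄)) + 0.842·√(p₁q₁ + p₂q₂)]² / (p₂−p₁)², with p̄ = 0.115.

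- 1.96·√0.20355 = 0.884 and 0.842·√0.1995 = 0.376.
- (0.884 + 0.376)² / 0.09² ≈ 196.1, rounded up to **197 per group**, as stated.
- 480 recruited less 15% leaves 408, or 204 per group, with power 0.815.

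The sample size is correct on its own inputs.

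**2. The same readings in each arm.**

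| BP pattern | Experimental | Control |
|---|---|---|
| Mean below 140/90 for three days | Drug stopped | No rule; drug continues |
| Back at or above 140 and/or 90 for one month | Prior drug restarted | No rule |
| At or above 160 and/or 100 for three days | Drugs added | Drugs added |

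**3. What the contrast contains.** Write A for the change in recurrence from acupuncture with drugs handled as in control, and W for the further change from the stop/restart rule. The trial estimates D = A + W. It has no arm that separates the two.

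**4. Illustration (assumptions, not in the documents).** Take 7% as the experimental rate with the drug continued. Let a fraction f stop, with recurrence 7% × RR. The experimental rate is then 7% × (1 − f + f·RR). Control is 16%, with 197 per group.

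| f | RR | Experimental rate | Power |
|---|---|---|---|
| any | 1.0 | 7.00% | 0.80 |
| 0.25 | 1.5 | 7.88% | 0.70 |
| 0.50 | 1.25 | 7.88% | 0.70 |
| 0.50 | 1.5 | 8.75% | 0.59 |
| 0.50 | 2.0 | 10.50% | 0.36 |

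In the row f = 0.50, RR = 1.5: A = 7 − 16 = −9 points, W = 8.75 − 7 = +1.75, and D = −7.25. The same D arises if A = −7.25 and W = 0. The trial's data cannot tell these apart. The article does not say whether its 7% already allows for stopping, so the table shows sensitivity and is not a corrected power.

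**5. How many might stop.** No share is given. With 1:1 allocation, 480/2 = 240 per arm. An assumed 20–50% gives 240 × 0.20 = 48 to 240 × 0.50 = 120. Among the 204 left after 15% dropout, it is about 41 to 102.

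**6. The sole-acupuncture subset.** Exclusion criterion 3 removes patients already below 140/90 on one drug, so everyone enters at or above the threshold on at least one component. Regression to the mean could bring some below it without any treatment effect. Those patients would then form the acupuncture-only group, with no randomised counterpart.

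**7. After week 12.** Acupuncture runs for 12 weeks, and the primary outcome is counted over the following 9 months. A patient on acupuncture alone at week 12 may enter that window on neither treatment until a restart or escalation condition is met. The Follow-up section then advises antihypertensives when BP is at or **below** 160 and/or 100 for one month. That does not fit the medication adjustment section, where the triggers are readings at or **above** a threshold.

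**The case against.** The best defence is that this is a disclosed, pragmatic choice. The article states the stopping rule openly, says throughout that drugs follow BP, and plans an intention-to-treat analysis. Comparing two management strategies is a legitimate question. All of that stands: the comparison is valid for the strategies. What it does not do is make the strategy effect the add-on effect named as the objective.

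Stronger readings a reader might infer are not supported:

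- **That the trial cannot show any add-on benefit.** If stopping the drug does not itself help, withdrawal works against the experimental arm and a favourable result is conservative. That condition is unproven here. The Background credits one drug combination with benefits beyond BP lowering and also cites a J-shaped relation between BP and recurrence, so the direction of W is not settled.
- **That control is fixed single-drug treatment.** Table 2 and the adjustment section allow it to change with BP.
- **That stoppers go untreated for the whole 9 months.** The restart and escalation rules, the diaries and the monthly calls all apply. Only a patient who never meets a condition would remain on neither treatment.
- **That a regression-to-the-mean analysis is planned.** The statistical section lists no analysis of patients whose drug was stopped. The problem lies in the aim, which has no valid comparator.
- **That subject blinding is necessarily lost.** Stopping a drug reveals the arm only to a patient who knows that the rule is arm-specific, and the article does not say that patients are told this. Its Discussion already lists as a weakness that some patients will probably know their group. The claim that blinding is ensured is still too strong beside that concession.

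**Conclusion.** The point holds as a mismatch between objective and contrast. Drug stopping below 140/90 mmHg applies to one arm only, so the randomised comparison estimates the effect of a strategy.

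- A null or adverse recurrence result, or similar BP at weeks 6 and 12, could conceal an add-on benefit offset by withdrawal.
- A favourable result supports an add-on benefit only on the assumption that stopping does not itself help.
- Any pure or sole acupuncture result is non-randomised.

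The size cannot be fixed from the documents. The range of 48–120 patients and the power figures rest on assumed stopping shares and risk ratios. Neither the sample size nor the validity of the intention-to-treat analysis for the strategy is in question. The change is advisable because it alters what the trial can conclude.

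**What to change.** 1. Restate the objective and conclusion as HuoXueSanFeng acupuncture with BP-triggered stopping, restarting and escalation of antihypertensives, versus continued antihypertensive treatment with BP-triggered escalation, both on routine stroke care. Describe control as BP-adjusted. Keep the intention-to-treat analysis regardless of drug changes.
2. Label any pure or sole acupuncture result descriptive and non-randomised.
3. Report antihypertensive use by arm beside each BP comparison and beside the primary result.
4. Replace the statement that needling both groups ensures subject blinding with wording consistent with the Discussion, noting that arm-specific drug stopping is a possible cue to allocation.
5. Have the clinical team reconcile Study design and setting, Experimental group, Antihypertensive medication adjustment and Follow-up on what applies after week 12 to a patient on acupuncture alone, including the direction of the Follow-up thresholds. No clinical rule is proposed here.

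The cost is small. Items 1, 2 and 4 are wording, and the data for item 3 are already recorded on the Case Report Forms. Item 5 needs a clinical decision. The downside is a narrower headline claim.

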### Control group

The control group will receive one antihypertensive medication on the basis of ischemic stroke routine care. In our trial, basic ischemic stroke medical care includes 12 weeks of *XingNaoKaiQiao* needling therapy plus other forms of routine stroke care. Twelve weeks of *XingNaoKaiQiao* needling therapy should also aid in the improvement of compliance in both groups for its high acceptance and remarkable effectiveness for stroke. All medications must be recorded in the drug combination form, including the types, dosage, usage frequency and time, etc., in order to provide data for analysis and the report summary. The acupuncture needle is the same with that used in *HuoXueSanFeng* acupuncture treatments. The acupoint locations and manipulations are presented in Table 3. No common acupoints are used in the two formulas. The retention time and frequency of treatments are identical to *HuoXueSanFen*g acupuncture therapy. During the entire process of our study, the control-group patients are prohibited from receiving any BP-lowering acupuncture therapy, and any violations will be recorded.

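### The objective names an add-on effect on stroke recurrence, but the randomised contrast is acupuncture with blood-pressure-triggered drug withdrawal versus continued drug

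*Protocol article*

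**What the plan says.** **The label.** The last paragraph of the Background sets the primary objective: to "determine whether BP-lowering acupuncture add-on therapy could decrease the recurrence of first-time ischemic stroke in patients during the 9-month follow-up period". The abstract's background and closing aim also speak of add-on acupuncture. The Experimental group section describes HuoXueSanFeng as given on top of what controls receive. Table 2 lists one antihypertensive drug in both arms, adjustable by BP level.

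**The drug rules.** One paragraph before the objective, the Background says: "The difference between the control and experimental groups is that in our experimental group", after a period of acupuncture and once BP is below 140/90 mmHg, "the prior antihypertensive drugs will be ceased, so as to observe the clinical effects of pure acupuncture on BP". The section on antihypertensive medication adjustment gives the working rule for that arm: "if the patients have a mean BP level below 140/90 mmHg for three consistent days, they will receive solely acupuncture treatment". If BP then stays at or above 140 systolic and/or 90 diastolic for 1 month, "prior antihypertensive medications should be re-dispensed". Both arms step up after three days at or above 160 and/or 100 mmHg. For controls that is the only rule: "other antihypertensive drugs will be prescribed in the opinion of the treating physicians, and these will be documented for final analyses". The control arm's basis is stated as "The control group will receive one antihypertensive medication on the basis of ischemic stroke routine care".

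**The timing.** Both needling regimens last 12 weeks. The primary outcome is recurrent stroke over the 9 months after those 12 weeks (Study design and setting; Outcome assessments). It is compared by chi-square or Fisher's exact test in intention-to-treat and per-protocol sets.

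**The concern.** An add-on question asks what happens when a treatment is placed on top of a background that is the same in both arms. Here the background is made to differ. A control patient and an experimental patient with the same three days below 140/90 mmHg are handled differently: the first keeps the drug and the second stops it.

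The stop has its own stated purpose, which is to see what acupuncture alone does to BP. It is nonetheless built into the comparison for stroke recurrence, in patients whose stroke was 2 to 6 weeks before entry and for whom the Background calls hypertension an independent risk factor for recurrence.

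What is at stake is the sentence that will report the primary result. A non-significant result worded as showing that add-on acupuncture does not reduce recurrence would be unsound, because any effect of acupuncture and any effect of stopping the drug in one arm cannot be separated. A significant result would support the strategy as run, and should be worded that way.

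**Working it through.** The plan gives no figure for this point, so the check sets the treatment rules side by side.

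**Step 1. Entry.** Patients are on one antihypertensive drug with BP below 160/100 mmHg, and those already below 140/90 mmHg on that drug are excluded (Inclusion criteria; Exclusion criteria). Everyone therefore starts on drug and above the stop threshold.

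**Step 2. Rules by arm.**

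| Element | Experimental | Control |
|---|---|---|
| XingNaoKaiQiao acupuncture, 12 weeks | yes | yes |
| Routine stroke care | yes | yes |
| HuoXueSanFeng acupuncture, 12 weeks | yes | no |
| One antihypertensive drug at start | yes | yes |
| Drug stopped when mean BP is below 140/90 for three days | **yes** | **no rule** |
| Drug returned after 1 month at or above 140 and/or 90 | yes | not applicable |
| Step-up after three days at or above 160 and/or 100 | yes | yes |

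The arms differ in two elements, the HuoXueSanFeng acupuncture and the drug stop with its return rule. The objective names only the first.

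**Step 3. Who gets what in the experimental arm.** Patients who stay at or above 140/90 mmHg keep the drug and do receive add-on treatment. Patients who fall below it for three days move to acupuncture without the drug. The document does not say how many to expect of each.

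**Step 4. Treatment during the primary window.** Needling stops at week 12 and the 9-month count starts then. The medication adjustment section returns the drug only on a BP trigger and not because needling has ended. A responder who is off drug at week 12 therefore enters the window on neither HuoXueSanFeng nor drug. Under that section the gap lasts about 1 month if BP settles at 140–159 and/or 90–99 mmHg, and can last the whole window if BP stays below 140/90 mmHg. The Follow-up section has another rule, under which drugs are advised after 1 month at or below 160 and/or 100 mmHg. Read literally, it would end the gap after about a month, but it does not fit the adjustment section. The typical drug-free time therefore cannot be fixed from the document.

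**Step 5. What intention-to-treat estimates.** Analysed as randomised, the contrast is 12 weeks of HuoXueSanFeng with BP-triggered, reversible drug withdrawal, against continued drug with step-up at 160/100 mmHg. That is a well-defined treatment-strategy effect. It would equal the effect of adding acupuncture to maintained drug only if stopping the drug had no effect on recurrence, which the document neither shows nor assumes.

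**Step 6. Sample size.** This is not in dispute. For 16% versus 7%, two-sided 5% and 80% power, the pooled-variance formula n = [1.960·√(2·0.115·0.885) + 0.842·√(0.16·0.84 + 0.07·0.93)]² / 0.09² gives 197 per group after rounding up, as stated. Nothing above changes that figure.

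**The case against.** The strongest reply is that the article defines its own term. The stop is introduced as the difference between the arms, with trigger and purpose, immediately before the objective. Read in order, the add-on therapy is the regimen just described. Comparing strategies is legitimate in a pragmatic trial. All experimental patients start with acupuncture on top of the drug, and some stay on both. The abstract says medication will be adjusted by BP, and the detail belongs in the methods. Medication changes are already recorded.

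Much of this stands. The stop is disclosed, the comparison is valid, and the records exist. But disclosure in one paragraph does not make the objective match the contrast. The abstract's general sentence on adjustment suggests a rule common to both arms, and the Experimental group section describes a pure addition. A reader of those parts would take the result as an effect of acupuncture over and above the drug.

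Two stronger readings are tempting and neither is supported.
- A reader might infer that the withdrawal raises stroke risk and so biases the trial towards no difference or costs it power. The document gives neither the time off drug nor the risk off drug. Under the adjustment section an off-drug patient is below 140/90 mmHg, has been above it for less than a month, or steps up at 160/100 mmHg, while controls may stay at 140–159/90–99 mmHg without further drugs. Worse BP control than in controls is therefore not shown, and any power figure would rest on invented inputs.
- A reader might infer that the comparison is confounded or the stop hidden. It is neither: the stop is part of a randomised strategy and is stated openly.

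**Conclusion.** The point holds as a mismatch between the stated objective and the contrast that the treatment rules create. It is of moderate weight and should be fixed. Intention-to-treat estimates the composite strategy and supports no separate statement about acupuncture added to maintained drug therapy.

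This rests only on rules stated in the article: the stop in one arm, its reversal rule, the end of needling at week 12, and the 9-month window after it. It does not depend on how many patients stop the drug, for how long, or with what effect. Because those quantities are not given, the direction and size of any withdrawal effect on recurrence cannot be stated.

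**What to change.** 1. Restate the primary objective, the abstract's aim and the Table 2 aim along these lines: to compare, for stroke recurrence over the 9 months after treatment, 12 weeks of HuoXueSanFeng acupuncture with BP-triggered, reversible withdrawal of the antihypertensive drug, versus continued drug with step-up at 160/100 mmHg, with both arms on XingNaoKaiQiao acupuncture and routine stroke care.
2. Limit the conclusion to that strategy, whether the result is significant or not.
3. Beside the primary result, report time off antihypertensive drug by arm within the 9-month window. The data are already required: "All medications must be recorded in the drug combination form", adjustments go into the case report forms, and Table 1 has them recorded at any time. This should be descriptive only, since time off drug arises after randomisation and depends on BP response.

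The cost is amendment wording and one table. Randomisation, endpoint, test, sample size and data collection do not change. The downside is a narrower claim than the add-on label suggests.
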